#### 2.5.5 Recovery modalities

##### 2.5.5.1 Trunk stabilization exercises

The TSE program will consist of (a) Front Plank; (b) Back Bridge; and (c) Quadruped Exercise. Okubo et al. (2010) reported that the trunk stability exercises employed in this study elicit greater activation of local muscles compared to other exercises.

During the front plank exercise, participants will assume a prone position, supporting their body weight with their toes and forearms. From this position, they will lift their right arm and left leg simultaneously, holding them straight for 5 seconds. Then, they will switch to lift their left arm and right leg for another 5 seconds. Afterward, participants will lower their body to the floor and rest for 10 s. This exercise will be repeated five times (Imai et al., 2014a).

During the quadruped exercise, participants will be placed in a four-legged position. They will focus on keeping their pelvis neutral and breathing normally. They will lift their right arm and left leg together, holding them straight for 5 seconds. Then, they will lift the left arm and right leg similarly. After each set, they will rest for 10 s. This exercise will be repeated five times (Imai et al., 2014b).

During the back bridge exercise, participants will lie supine on the floor with their feet flat, knees bent at a 90-degree angle, toes facing forward, and hands folded over their chest. They will raise their pelvis to attain and sustain a neutral hip flexion angle, then elevate one leg off the floor and straighten the knee. This posture will be held for 5 seconds. Subsequently, they will lift the other leg, maintaining the position for 5 seconds. A rest of 10 s will follow. This exercise will be repeated five times (Imai et al., 2014a).

##### 2.5.5.2 Foam rolling exercises

Participants will perform the foam roller exercise targeting the lower extremities and back, focusing on muscles such as the hamstrings, quadriceps, IT band, calves, rhomboids, and latissimus dorsi. They will roll the foam cylinder along each selected area for 30 s, moving from the top of the muscle group to the starting position (Healey et al., 2014).

Quadriceps. For quadriceps, participants lie face down and position the foam roller under their thighs. Their forearms rest on the floor in a plank position. While supporting some of their body weight, participants roll the foam roller distally and proximally from the hip bottom to the knee top (Healey et al., 2014).

Hamstrings and the calves. To target the hamstrings and calves, participants sit with the roller beneath their upper thighs or calves. Their hands are positioned on the floor with fingers facing toward their body. They roll the roller distally and proximally from just below the greater trochanter to just above the knee, or from just below the knee to just above the ankle, while partially supporting their body weight with their hands (Healey et al., 2014).

IT band. For the IT band, participants roll the foam roller while lying on their side. They cross one leg in front of the other and slightly raise the lower leg off the floor. The rolling motion spans from just below the greater trochanter to just above the knee joint (Healey et al., 2014).

Latissimus dorsi. For the latissimus dorsi, participants lie on their side with one arm stretched overhead and the foam roller positioned in the armpit region. Minimal movement is involved in this technique (Healey et al., 2014).

Rhomboids. To target the rhomboids, participants lie on their back with arms crossed and the foam roller positioned beneath their shoulders. They lift their hips off the floor and roll the foam roller downward and upward, from shoulder level to the middle of the back (Healey et al., 2014). The multilevel rigid roller (MRR) will be used in this study (Curran et al., 2008).

##### 2.5.5.3 Passive recovery

Participants will be required to do nothing and lie on a bed in a darkened room for a duration of 24 min between the pretest and posttest assessments (Seidi et al., 2019).

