#### 2.5.2 Experimentation

The experiment involves 20 participants, each completing three sessions spaced 1 week apart. In each session, they will perform a modified Abt’s fatigue protocol, consisting of eight exercises targeting their core muscles. Subsequently, they undergo recovery modalities. Everything will remain the same throughout the sessions except the type of recovery modality, which will be varied (trunk stabilization exercises, foam rolling exercises, and passive recovery). The order of the recovery modalities will be counterbalanced to control for potential sequence effects. Data will be gathered from participants at three different time points:1. Pre-fatigue assessment (baseline measurement).2. Post-fatigue assessment (immediately following the fatigue protocol).3. Post-recovery modalities assessment (immediately and 15 min after the completion of active and passive modalities, respectively).

Participants will be tested by the same examiners at the same time.

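### Passive recovery runs about 19 min longer than trunk stabilization, so active-versus-passive contrasts at the same assessment label mix modality with time since fatigue

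*Protocol article*

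**What the plan says.** Each participant attends three sessions a week apart, with the order of modalities counterbalanced. Section 2.5.2 says of these sessions: "Everything will remain the same throughout the sessions except the type of recovery modality, which will be varied".

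The lengths of the modalities have to be read from their descriptions:

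- **Passive recovery (2.5.5.3):** participants "lie on a bed in a darkened room for a duration of 24 min between the pretest and posttest assessments".
- **Trunk stabilization (2.5.5.1):** "The TSE program will consist of (a) Front Plank; (b) Back Bridge; and (c) Quadruped Exercise". One repetition of the front plank has two 5 s holds, one for each diagonal arm-and-leg pair, and ends with a pause: "Afterward, participants will lower their body to the floor and rest for 10 s. This exercise will be repeated five times". The other two exercises follow the same pattern.
- **Foam rolling (2.5.5.2):** "They will roll the foam cylinder along each selected area for 30 s". Six muscle groups are named. The number of sets, and whether each side is rolled separately, are not stated.

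Section 2.7 defines T3 and T4 as 0 and 15 min after the end of the modality, for all three conditions. Sections 2.5.3.1 and 2.5.3.2 also give both post-recovery times without distinction by condition. Section 2.5.2 words it differently: "immediately and 15 min after the completion of active and passive modalities, respectively".

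Passive recovery is one of the three levels of the condition factor in the two-way ANOVA. In the nonparametric alternative, conditions are compared at each testing time.

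**The concern.** The outcomes are acute measures taken after induced fatigue: EMG frequency and amplitude, sway and flexibility. Such measures can be expected to drift back toward baseline with rest alone. A passive session is useful as a control because it shows how much of the recovery time alone accounts for, and for that the clock must read the same in every session. Here T3 and T4 are tied to the end of modalities of very different length, so the same label stands for different times since fatigue.

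The active-versus-passive comparison is at stake. The introduction hypothesizes that both exercises improve core and postural stability, and the abstract that they are equivalently effective. Similar results in the two active sessions cannot separate two effective exercises from two that add nothing to the passage of time. That distinction depends on the passive session. Counterbalancing the order does not help, because length is tied to modality in every session.

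**Working it through.** **Check of the timing method on a stated total.** Section 2.5.4 gives four cycles of eight exercises, each 40 s of work and a 20 s pause: 4 × 8 × (40 + 20) s = 1,920 s = 32 min. This reproduces the stated 32 min.

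**Modality durations.**

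- Trunk stabilization: 3 exercises × 5 repetitions × (5 + 5 + 10) s = 300 s = 5 min (4.8 min without the final rest).
- Foam rolling, one pass per area: 6 × 30 s = 3 min. If all areas are rolled on each side, 12 × 30 s = 6 min.
- Passive: 24 min, as stated.

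Transition times are not given and are taken as zero.

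**Minutes from the start of recovery** (T3 = duration; T4 = duration + 15):

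| Session | T3 | T4 |
|---|---|---|
| Trunk stabilization | 5 | 20 |
| Foam rolling (one pass) | 3–6 | 18–21 |
| Passive | 24 | 39 |

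Gap between passive and trunk stabilization: 24 − 5 = 19 min at T3 and 39 − 20 = 19 min at T4. Gap between passive and foam rolling: 18–21 min. Passive T3 at 24 min comes after T4 of both active sessions. The two active modalities differ by at most 2 min. The T2 battery comes before recovery in every session, so it does not change these differences if it takes equally long each time.

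**Sensitivity to the foam-rolling details.** An assumed three passes gives 9–18 min, which still leaves a gap of 6–15 min to passive. The 19 min gap for trunk stabilization does not depend on this.

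**Possible size of the bias.** The article gives no recovery rate. Assume exponential recovery with half-time *h* and no modality effect. The share of the deficit present at the start of recovery that has resolved by time *t* is 1 − 0.5^(t/h).

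| Assumed *h* (min) | 5 | 10 | 15 | 30 |
|---|---|---|---|---|
| Trunk stabilization T3, t = 5 | 50% | 29% | 21% | 11% |
| Passive T3, t = 24 | 96% | 81% | 67% | 43% |
| **Difference at T3 (points)** | **46** | **52** | **46** | **32** |
| Trunk stabilization T4, t = 20 | 94% | 75% | 60% | 37% |
| Passive T4, t = 39 | 99.6% | 93% | 84% | 59% |
| **Difference at T4 (points)** | **6** | **18** | **23** | **22** |
| Passive T3 (24) minus trunk stabilization T4 (20) | 3 | 6 | 7 | 6 |

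Differences are computed before rounding. The last row shows that the nearest time-matched pair already in the schedule leaves 3–7 points under the same assumption.

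**The case against.** **The main comparison is active against active.** The stated purpose is trunk stabilization versus foam rolling, and the discussion treats the superiority of active recovery as widely accepted. This stands. A reader might infer from the 19 min gap that the whole modality factor is compromised. The figures do not support that, because the two active modalities differ by at most about 2 min when each area is rolled once. The problem lies in the contrasts with passive recovery and in the overall tests that include it.

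**The control is not worthless.** A reader might also conclude that the passive session can show nothing about whether exercise helps. That goes too far. If time favours passive recovery, an active advantage at T3 despite about 19 fewer minutes would still be evidence of benefit. Only a null or passive-favouring result is uninterpretable.

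**The magnitudes are assumed.** This stands. The half-times are not from the article, one curve is applied to EMG, sway and flexibility alike, and any recovery during the T2 battery makes the deficit at the start of recovery smaller than the deficit at the end of fatigue.

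**Foam-rolling time is not fixed.** This also stands. A condensed article may leave sets and sidedness to the full protocol, so only the trunk-stabilization gap is firm.

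**Length may be part of the modality.** Sessions of unequal length can be compared as packages. But section 2.5.2 says that only the type of modality varies, and a package comparison would not isolate what exercise adds to time.

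**The wording in section 2.5.2.** Read literally, active modalities would be assessed immediately and passive recovery only at 15 min, which widens the gap to 33–36 min (39 minus 3–6). The other sections give both times for every condition, so this is a wording conflict to reconcile and not a larger bias.

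**Conclusion.** The point holds for active-versus-passive contrasts at the same label, and for the condition main effect and condition-by-time interaction that include passive recovery. On the stated figures, passive T3 and T4 fall about 19 min later after fatigue than in the trunk-stabilization session. This conflicts with the claim that only the type of modality changes, and the article describes no matching or adjustment.

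The direction of the bias, in favour of passive recovery, rests on fatigue resolving with time. Its size is unknown; the calculated range shows only that it could be large at T3 and smaller but not negligible at T4. For foam rolling, the 18–21 min gap assumes one pass per area. The trunk-stabilization versus foam-rolling comparison is little affected.

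**What to change.** 1. Keep the immediate T3 for the trunk-stabilization versus foam-rolling comparison. Moving it to a common clock time would give up the immediate effect that the study sets out to measure.
2. Record the time from the end of the fatigue protocol to each assessment in every session.
3. Base active-versus-passive conclusions on assessments at the same elapsed time since fatigue in all three sessions.
4. If the schedule is left as it is, name active T4 (about 20 min) versus passive T3 (24 min) as the active-versus-passive contrast. State the caveat that active T4 follows one extra test battery, which includes maximal contractions. Do not interpret T3 against T3, or T4 against T4, versus passive as a pure modality effect.
5. Reconcile the durations in section 2.5.5 with the statement in section 2.5.2 that all else stays the same, and the assessment wording in section 2.5.2 with sections 2.5.3 and 2.7. Which durations to use is for the investigators to decide.

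**Cost.** Wording changes and a time stamp, with no extra participants. A matched assessment adds some laboratory time to the active sessions: reaching passive T4 would take about 19 min beyond trunk-stabilization T4 (39 − 20). Without one, the match stays imperfect, by about 4 min and one test battery for trunk stabilization.

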### 2.6 Data management

The study will encompass the collection of individual demographic data and outcome data. The data from the questionnaire will be entered into a database, where the study team will check its accuracy before utilizing it. All information and outcome data will be securely stored on computers with password protection, accessible solely by the study team. Throughout and following the completion of the project, data management will outline the methods for collecting, documenting, storing, and preserving data.

### 2.7 Statistical analysis

The statistical analysis will employ SPSS Statistics software (Version 24; IBM Corporation^©^, United States). To evaluate the normality of core and postural stability, as well as EMG variables, a Shapiro-Wilk test will precede any comparative analyses. For normally distributed data, a two-way ANOVA will be applied to explore the main effects of recovery modalities and time intervals, along with any potential interactions between these factors. The factors under consideration include the type of conditions [trunk stabilization exercises session, foam rolling exercise session, passive recovery] and testing time [T1: baseline, T2: immediately after modified Abt’s fatigue protocol, T3: immediately after recovery modalities, and T4: 15 min after recovery modalities]. To identify significant differences, Bonferroni *post hoc* comparisons will be conducted as necessary.

For non-normally distributed data, nonparametric tests will be utilized. Friedman’s test, followed by Dunn’s *post hoc* test, will be employed to compare core and postural stability, as well as EMG variables across testing times [T1, T2, T3, and T4]. The Kruskal-Walli’s test will be utilized for between-condition mentioned above comparisons at each testing time.

Data will be presented as mean ± standard deviation (SD). Effect sizes for both between-session and within-session comparisons of all quantitative variables will be evaluated using Cohen’s d coefficient: small effect (d < 0.2 and ηp2 = 0.01); moderate effect (d ≈ 0.5 and ηp2 = 0.06); and large effect (d > 0.8 and ηp2 = 0.14) (Cohen, 2013). The significance level (α) will be established at 0.05 for all statistical tests.

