### 2.4 Sample size estimation

Sample size estimation was conducted utilizing the G*Power software package (version 3.1.9.7) based on the methodology outlined in the study by Fonta et al. (2021). The input parameters included the following: the statistical test was repeated measures, within factors; the α error probability was 0.05; the effect size F was 0.25; power (1 − β error probability) was 0.80; correlation among repeated measures was 0.70; and no sphericity correction (e = 1) was applied. It is important to note that the magnitude of the correlations (r = 0.7) can be considered large according to Hopkins et al. (2009). This correlation was chosen to reflect the anticipated relationship between the repeated measures in this study, based on the literature (Hopkins et al., 2009; Fonta et al., 2021; Zahiri et al., 2022). Consequently, the total sample size was determined to consist of seven subjects (in each trial). To ensure ample statistical power, especially in scenarios with smaller-than-expected effects or lower correlations between repeated measures, we decided to include 20 participants, who will be tested in the three experimental conditions. This approach also takes into account the possibility of participant dropouts during the study.

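### A Shapiro-Wilk pre-test sends some outcomes to a rank branch that has no modality-by-time interaction test and compares paired crossover data with an independent-groups test

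*Protocol article*

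**What the plan says.** All of this is in the protocol article.

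- **Pre-test.** Section 2.7 states that "a Shapiro-Wilk test will precede any comparative analyses". The variables it names are core and postural stability and EMG.
- **Branch if normal.** "For normally distributed data, a two-way ANOVA will be applied". It covers both main effects and, in this branch only, the interaction ("along with any potential interactions between these factors"). The factors are three modalities and four times (T1 baseline, T2 after fatigue, T3 immediately after recovery, T4 15 minutes later).
- **Branch if not normal.** Friedman, then Dunn, compares the four times. For modalities, a Kruskal-Wallis "test will be utilized for between-condition mentioned above comparisons at each testing time".
- **Alpha.** The level "will be established at 0.05 for all statistical tests".
- **Design.** Section 2.4: "we decided to include 20 participants, who will be tested in the three experimental conditions". Section 2.5.2 confirms three sessions per person, one week apart.

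**The concern.** The study asks whether recovery from induced fatigue differs between modalities. With T1 to T4 measured in every session, the test that addresses this directly is the modality-by-time interaction, and only the ANOVA branch contains it. Whether an outcome gets that test therefore turns on a significance test of normality, which rejects some truly normal outcomes by chance. Related sway and EMG variables could then be judged by different methods.

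The rank branch has a second, separate fault. Kruskal-Wallis assumes independent groups, but the three modality columns come from the same people. When values within a person are positively correlated, this test measures modality differences against between-person spread, which the design was chosen to remove. It then rarely rejects. That matters more here because the abstract hypothesises that the two exercises are equally effective, so a non-significant result from an insensitive test could easily be misread as support.

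**Working it through.** **Inputs from section 2.4:** n = 20, f = 0.25, r = 0.70, alpha 0.05, power 0.80, no sphericity correction. **Assumptions, not in the documents:** normal data, compound symmetry at r = 0.70 over all 12 modality-by-time values, two modalities equal and the third different at T3 and T4. The two-way ANOVA is read as repeated measures, in line with section 2.4.

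**1. The plan's own figure.** The stated size is seven per trial.
- With the noncentral F for a within-between interaction with 3 groups and 4 measurements, N = 19 gives power 0.810. Rounded up to equal groups this is 21, and 21 / 3 = 7, an exact match.
- A one-group within-factor calculation uses lambda = f² × N × m / (1 − r). With m = 12 measurements it needs N = 8 (power 0.825; N = 7 gives 0.748).
- For the 20 people planned and m = 3, lambda = 0.0625 × 20 × 3 / 0.30 = 12.5 and power is 0.87. This checks the simulated repeated-measures F in step 3.

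**2. Effect pattern.** For means (0, 0, d) in SD units, f = d × √2 / 3, so d = 0.25 × 3 / √2 = 0.53 SD.

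**3. Simulation of each test** (20,000 data sets per setting, n = 20):

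| Test | Power, r = 0.70 | Power, r = 0.50 |
|---|---|---|
| Kruskal-Wallis at T3 (planned rank branch) | 0.216 | 0.25 |
| Friedman across modalities at T3 (paired) | 0.75 | 0.52 |
| Repeated-measures F at T3 | 0.87 | 0.65 |
| Repeated-measures modality-by-time interaction | 0.74 | 0.47 |

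A separate run of 6,000 data sets at r = 0.70 gave 0.211 for Kruskal-Wallis and 0.864 for the repeated-measures F. With no true difference, Kruskal-Wallis rejects at a rate of about 0.0002 at r = 0.70 and 0.004 at r = 0.50, against a nominal 0.05. The reason is simple: differences between modality means carry only 1 − 0.70 = 0.30 of the variance that an independent-groups test allows for.

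**4. Source of the loss at r = 0.70.** The total drop is 0.87 − 0.21 = 0.66. Ignoring the pairing accounts for 0.75 − 0.21 = 0.54 of it, and using ranks for 0.87 − 0.75 = 0.12.

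**5. Share of truly normal outcomes that fail the pre-test.** This depends on what is tested, which the article does not say.
- One test on model residuals: about 5%.
- The three modalities at one time: 1 − 0.95³ = 14%.
- Any of the 3 × 4 = 12 cells: 1 − 0.95¹² = 46% if independent. Simulated values are 46% at r = 0.50, 41% to 42% at r = 0.70 and 38% at r = 0.80.

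**6. Power of the one-time modality comparison under the whole rule**, r = 0.70, truly normal outcome. This is a simple mixture that treats the pre-test result as unrelated to the later test:
- 5%: 0.95 × 0.864 + 0.05 × 0.211 = 0.83
- 14%: 0.86 × 0.864 + 0.14 × 0.211 = 0.77
- 42%: 0.58 × 0.864 + 0.42 × 0.211 = 0.59

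With the paired Friedman test across modalities in the rank branch, the last line becomes 0.58 × 0.864 + 0.42 × 0.75 = 0.82. The interaction would still be untested in that branch.

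**The case against.** The strongest reply is that this is a condensed article and the full plan may say what the pre-test is applied to. With one test on residuals, only about 5% of normal outcomes are diverted and the rule loses little. This stands as a limit on size. A reader might infer that nearly half of all normal outcomes will be misrouted, but that holds only if any one of 12 cells can divert an outcome, and the article does not say so.

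Second, the power loss should not be blamed on the pre-test. This also stands: most of it comes from the unpaired test, which would be wrong for this design with or without a pre-test.

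Third, the rank branch is not silent on modality. The purpose is to compare immediate effects, so a comparison at T3 is relevant. That is fair. What is wrong is that the comparison is unpaired and takes no account of each person's earlier values.

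Three other stronger readings are not supported:
- **The whole rank branch lacks power.** Friedman over time keeps the pairing, and Kruskal-Wallis reaches 0.74 at a difference of 0.8 SD (0.02 at 0.3, 0.17 at 0.5, 0.35 at 0.6; r = 0.70).
- **Flexibility outcomes follow the same route.** Section 2.7 does not name them in the pre-test or Friedman sentences.
- **Skewed outcomes failing the pre-test are misrouted.** Rejecting those is what the pre-test is for, and the article gives no spread from which to say how often it would happen.

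**Conclusion.** The point holds in this form. Section 2.7 fixes an explicit rule under which core stability, postural stability and EMG outcomes judged non-normal get no interaction test and an independent-groups comparison of paired data. Neither feature depends on anything left to an unseen plan.

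For an outcome that reaches the rank branch, power of the one-time modality comparison is about 0.21 where a paired test would have 0.75 to 0.87, with a type I error near zero. Over the whole rule it is about 0.83 at best and 0.59 at worst, depending on the unstated unit of the pre-test. These sizes rest on the protocol's f and r, one assumed effect pattern, normal data and compound symmetry. The direction is firm; confidence in the exact figures is moderate. The change should be made before analysis.

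**What to change.** Delete the Shapiro-Wilk pre-test and the Kruskal-Wallis branch from section 2.7. In their place:

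- Analyse every outcome with one within-person model containing modality, time, modality by time, and participant, so that the interaction is always tested.
- Check residuals with plots, not with a significance test.
- Name in advance the positive measures expected to be skewed and analyse them on the log scale.
- As a sensitivity analysis, permute modality labels within participant, moving whole sessions so that the four time values stay together.

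The cost is a reworded section and slightly more analysis work. It needs no extra participants, visits or measurements.

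### The trial is sized for a repeated-measures test, but section 2.7 names only a two-way ANOVA and never says that condition and time are within-participant factors

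*Protocol article*

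**What the plan says.** **Sizing (Protocol article, 2.4 Sample size estimation).** The calculation states that "the statistical test was repeated measures, within factors", that "the α error probability was 0.05", that "the effect size F was 0.25", that "power (1 − β error probability) was 0.80" and that "correlation among repeated measures was 0.70". No sphericity correction is applied (epsilon = 1). The result is 7 subjects, raised to 20 to cover smaller effects, lower correlations and dropout.

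**Design (2.5.2 Experimentation).** "The experiment involves 20 participants, each completing three sessions spaced 1 week apart". The recovery modality changes from session to session, and its order is counterbalanced.

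**Analysis (2.7 Statistical analysis).** "For normally distributed data, a two-way ANOVA will be applied to explore the main effects of recovery modalities and time intervals". The interaction is to be examined too. The factors are condition (3 levels) and testing time (T1 to T4), with Bonferroni comparisons afterwards. The section mentions neither a participant term nor a within-participant factor. For non-normal data it uses Friedman's test across times, which is for related samples, but Kruskal-Wallis between conditions, which is for independent samples.

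**The concern.** The test that was sized and the test that is named differ in their error term. A repeated-measures ANOVA removes stable differences between people and judges each effect against within-person variation. A two-way ANOVA with only condition and time as factors judges every effect against the spread between people inside each cell. It therefore gives up the correlation of 0.70 on which the stated power rests.

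The Kruskal-Wallis choice makes harmless shorthand harder to assume, because in that branch the section does treat three measurements on the same people as independent groups. An analyst who follows 2.7 to the letter could run an ordinary two-way ANOVA, or a mixed ANOVA with condition between participants. Either would give different p-values from the test in 2.4.

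The direction of the error matters. The Abstract hypothesises that the two exercises are equivalently effective. A test that hardly ever rejects tends to return non-significant modality differences, and readers could take these as support for that hypothesis.

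**Working it through.** **Inputs from the protocol.** alpha 0.05, f = 0.25, r = 0.70, epsilon = 1 and N = 7 raised to 20 (2.4); 3 conditions and 4 times, so m = 12 values per person (2.7).

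**Assumptions.** SD 1 and one common correlation r among all 12 values. The number of measurements entered in the sizing software is not printed, so m = 12 is also an assumption.

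**1. Reproduce the printed N.** For the 3 × 4 within-within interaction, λ = f²·N·m/(1 − r) with df 6 and 6(N − 1).
- N = 6: λ = 0.0625 × 6 × 12 / 0.30 = 15.0, power 0.748.
- N = 7: λ = 0.0625 × 7 × 12 / 0.30 = 17.5, power 0.836.

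So N = 7 is reproduced when f = 0.25 is the effect size of the full 12-cell interaction. A single within factor with 3 or 4 measurements gives 17 or 15 instead.

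**2. False-positive rate of the ANOVA as written, N = 20.** With no true effect, the interaction mean square has expectation 1 − r = 0.30, but it is divided by a within-cell mean square with expectation 1. The critical F on 6 and 12 × 19 = 228 df is 2.138. To exceed it, a chi-square on 6 df must pass about 2.138 × 6 / 0.30 = 42.8, which has probability about 1.3 × 10⁻⁷. In simulation the rejection rate was never above 0.0001, against 0.05 for the repeated-measures test.

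**3. Interaction power at N = 20, f = 0.25 over the 12 cells.** Repeated measures: λ = 0.0625 × 20 × 12 / 0.30 = 50, power above 0.999. ANOVA as written (simulated): about 0.77. At N = 7 the same comparison is 0.84 against 0.14.

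**4. A smaller-effect scenario.** Put f = 0.25 on the modality means at T3 and T4 only: −0.306, 0 and +0.306 SD, with equal means at T1 and T2. Check: √[(0.306² + 0 + 0.306²)/3] = 0.25. Half of this goes to the main effect and half to the interaction, so each has f = 0.125 over the 12 cells. Then λ = 0.015625 × 20 × 12 / 0.30 = 12.5. Simulated power at r = 0.70:

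| Analysis | Interaction | Modality main effect |
|---|---|---|
| Two-way repeated measures | 0.73 | 0.87 |
| Two-way ANOVA as written | 0.03 | 0.24 |
| Mixed ANOVA, condition between | 0.74 | 0.002 |

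In the same scenario, the largest Bonferroni modality contrast at T3 (alpha 0.05/3) has power 0.81 if paired and 0.23 with the pooled cell error. For r from 0.50 to 0.80, interaction power runs from about 0.47 to 0.91 with repeated measures, and from 0.07 to 0.01 as written.

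**5. Between the two scalings (N = 20, r = 0.70).** Interaction power, as written against repeated measures: f = 0.20, 0.38 against 0.99; f = 0.15, 0.08 against 0.89; f = 0.134, 0.04 against 0.80.

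**The case against.** The strongest reply is that the phrase is ordinary shorthand. Section 2.4 already places the test in the repeated-measures family, all 20 people pass through every condition, Friedman's test is used across times, and 2.7 speaks of between-session and within-session comparisons. A condensed article may also leave the exact error term to a fuller plan. This is a fair reading and may be what the sponsor intends. It does not settle the matter, because 2.7 does name a test, that test is not the sized one, and the same section assigns an independent-samples test to the conditions.

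The reply is right about the size of the loss. A reader might infer that the written ANOVA has almost no interaction power at the sizing's own inputs. The documents do not support that. With f = 0.25 on the scaling that reproduces N = 7, the written test still has about 0.77 power at the enrolled 20, just under the 0.80 target. The near-zero figures belong to effects around half that size, where even repeated measures reaches only 0.73.

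Nor does the interaction suffer under every departure from repeated measures. If only condition is treated as between-participant, interaction power is unchanged and the damage falls on the modality main effect. That main effect also averages over T1 and T2, before any recovery modality is given.

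**Conclusion.** The mismatch stands: 2.4 and 2.7 describe different tests, and the printed alpha and power belong only to the one in 2.4. Taken literally at N = 20 and r = 0.70, the ANOVA in 2.7 has an interaction false-positive rate of about 0. The power it loses depends on the effect: modest at the effect the trial was sized for, and severe for the smaller effects that the increase from 7 to 20 was partly meant to cover.

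These figures rest on a common correlation among all 12 values and unit SD, and on the stated reading of f. They do not show that the trial is too small. With the repeated-measures analysis, 20 participants give ample power at f = 0.25. They also do not show that the sponsor will run the wrong model, only that the current text permits it.

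**What to change.** In 2.7, replace the two-way ANOVA with a two-way repeated-measures ANOVA that has recovery condition (3 levels) and testing time (4 levels) both as within-participant factors. The equivalent linear mixed model, with participant and participant-by-session random effects, would also serve. State that the Bonferroni modality contrasts are paired within participant. In the non-normal branch, use a related-samples test between conditions, for the same reason.

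The cost is about a sentence in 2.7. No participants, visits or measurements are added, and the SPSS version already named can run the analysis. The analysis then matches the test in 2.4.
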